### 1.4. Anticipated Results

Considering the extant research (Colins et al., 2026; Goetz et al., 2024; Hawes et al., 2020; Neo et al., 2023; Molinuevo et al., 2020), it is anticipated that interrater reliability will range within the moderate-to-good range (*κ* = 0.50–0.90). Given that the clinician and the second coder are trained professionals (i.e., psychology master’s candidates, child and adolescent psychotherapists, and/or physicians) who have first observed two sessions to learn how to conduct and evaluate CAPE, it is expected that the study will also demonstrate moderate to high interrater reliability. However, the study’s double-blind design, which relies solely on written notes and visible checked items, with no audio or video recordings, might be a reason that interrater reliability will be significantly lower.

It is currently understood that approximately half of all children diagnosed with conduct disorders have an LPE, in line with previous studies (Colins et al., 2026; Kahn et al., 2013). If this is not the case, it might be attributable to the fact that, although this is a clinical sample with a diagnosed DBD, children exhibiting severe antisocial behavior may be unable to participate due to poor compliance. To understand this, the prevalence of LPE among children in outpatient settings was 21.6% in the most recent CAPE study (Neo et al., 2023). In contrast, in the detention center, it was 60% (Colins et al., 2026), indicating that prevalence can differ between settings.

It is hypothesized that, in terms of convergent validity, CAPE will be positively associated with proactive aggression. We also reckon that children and adolescents with LPE exhibit a higher symptom burden in DBD in both proactive and reactive aggression.

Regarding discriminant validity, it is predicted that patients with LPE will exhibit less developed social competence, empathy, parental warmth, and poorer emotional recognition. In addition, it is anticipated that the discriminant constructs will demonstrate a negative correlation with CAPE.

If the absence of LPE differentiation in proactive aggression and DBD symptom score remains, it may be attributable to aggressive behavior being a core symptom of a diagnosed conduct disorder, which could explain the observed variance. Conversely, LPE might exhibit greater divergence in neurological characteristics, such as emotion recognition (Díaz-Vázquez et al., 2024). Lack of advanced techniques, such as eye tracking, might hinder effective emotion recognition. The fact that we measure empathy globally and do not distinguish between affective and cognitive forms of empathy could explain the lack of a negative correlation (Frick & Kemp, 2021). Furthermore, it is hypothesized that, in the absence of LPE, parents will exhibit greater warmth. There are longitudinal data, particularly extending into middle childhood, that confirm this (Hyde et al., 2016; Tomlinson et al., 2022). However, given such a wide age range, this effect may diminish over time.

Thus, regarding incremental validity, it is hypothesized that CAPE might explain additional variance in the previously referenced convergent and discriminant constructs beyond that explained by the covariates of age and sex, as well as by the ICU. Should this not be the case, it might be attributable to CAPE administration being conducted exclusively with the primary caregiver. Consequently, a review of the child’s records and/or an interview with the child may not capture the full range of variation.

Furthermore, there might be little overall agreement between the primary caregiver’s and the child’s perceptions. This phenomenon may be attributed to the propensity of both children and parents to offer socially desirable responses. Notably, children with conduct disorders exhibit a distinct pattern of social–cognitive information processing and frequently perceive their own behavior as less aggressive (Crick & Dodge, 1994). This factor may also explain a potential lack of clear correlations between the primary caregiver’s rating and the child’s.

The distinction between primary and secondary CU traits is primarily evident in the domains of anxiety and the prevalence of abuse (Cecil et al., 2018; Todorov et al., 2025; Kimonis et al., 2012). Consequently, we assume children and adolescents with secondary CU traits will have higher levels of reactive aggression, poorer attention performance, higher parental strictness, lower parental warmth, higher emotion recognition, and, in general, significantly more pronounced DBD symptoms. This exploratory inquiry aims to determine the extent to which primary and secondary CU traits are also evident in a German clinical sample. The findings may indicate that there are no differences in parental strictness, as strictness may also be considered desirable when it is associated with consistent behavior (Kimonis et al., 2025). Furthermore, factors such as harsh or abusive parental behavior may be central to secondary CU traits, whereas strictness does not reflect this (Facci et al., 2024; Kimonis, 2023).

## 2. Materials and Methods

### 2.1. Setting and Design

This study is a multicenter, cross-sectional, clinical observational study using a case–control design. Data will be collected in outpatient, inpatient, and day-clinic settings of Child and Adolescent Mental Health clinics. The CAPE interview is conducted with the primary caregiver and evaluated by a clinician (LPE, yes/no). Standardized questionnaires are rated by the primary caregiver (external report) and the child (self-report).

### 2.2. Sampling Method, Recruitment, and Procedure

Participants are recruited from two independent clinical sites to improve the generalizability of results and to minimize potential site-specific biases. Parents of children/adolescents undergoing outpatient, inpatient, or day-clinic treatment, or who are on a waiting list for aggressive behavior treatment and diagnosed with DBD, will be contacted by telephone (Figure 1). If interested, study information and consent forms will be sent by post, and an appointment will be scheduled with the primary caregiver and child for data collection. The personal appointment at the Child and Adolescent Mental Health Department will last approximately 1.5 to 2 h. Participants and their primary caregivers are informed about the study, the voluntary nature of participation, data storage, and the procedural aspects involved. After the consent forms are signed, a trained clinician (e.g., a licensed child and adolescent psychotherapist or a trained physician) conducts the CAPE interview with the primary caregiver.

Additionally, the primary caregiver and child complete standardized questionnaires using the electronic data collection software SoSciSurvey^©^ (Version 3.5.07; Leiner, 2024) on a tablet. Due to the study’s format, completion of the study is contingent upon entering all data, thereby ensuring that no entries are missing. As part of the study, the questionnaires are read out to all children. They also have the opportunity to ask questions to make sure they understand. To reduce shared method variance and potential circularity in the validation analyses, SPJ are derived independently from the questionnaires. All families are offered a diagnostic and clarification phase for DBD regardless of their child’s LPE status on the CAPE. Each family is informed that they can share the CAPE results with their psychotherapist or physician.

### 2.3. Inclusion and Exclusion Criteria

Children and adolescents between the ages of 8 and 18 years who exhibit aggressive behavior symptoms above the cut-off (FBB-SSV; (Döpfner et al., 2017): total score ≥ Stanine 7) and who have been diagnosed with DBD (ICD-10: F90.1, F91, F92) will be included. Children and adolescents with acute psychotic symptoms, reduced intelligence (IQ ≤ 70), and a limited understanding of the German language (below C1) will be excluded.

### 2.4. Sample Size Calculation

In line with earlier findings (Colins et al., 2020; Goetz et al., 2024; Hawes et al., 2020; Molinuevo et al., 2020; Neo et al., 2023), we expect medium-to-large effect sizes for research question one when examining and comparing children with and without LPE across relevant convergent/divergent constructs (DBD and social competence, reactive/proactive aggressive behavior, emotion recognition, and empathy). Based on two groups (LPE, yes/no) in an analysis of covariance (ANCOVA), we can estimate, using G*Power 3.1 (effect size = 0.50, α = 0.05, 1−β = 0.95), that a total sample size of 55 would yield statistically significant results. We expect small-to-medium effect sizes when examining LPE correlations with relevant convergent/divergent constructs. Based on calculations (effect size = 0.40, α = 0.05, 1−β = 0.95), we can assume that a sample size of 63 patients would yield statistically significant results. In this context, moderate effects are also assumed when calculating incremental validity via hierarchical regression (effect size = 0.15, α = 0.05, 1−β = 0.95; number of tested predictors: 2; total number of predictors: 7), yielding an *N* of 83.

For research question two, children and adolescents with elevated CU traits will be separated into two groups based on whether they have primary or secondary CU traits, depending on at least two interpersonal potential traumatic events and high anxiety scores. Groups will be compared in levels of anxiety, depression scores, emotion recognition, empathy, DBD, and social competence, and reactive/proactive aggressive behavior (Bennett & Kerig, 2014; Craig et al., 2021; Craig & Moretti, 2019; Dadds et al., 2018; Kahn et al., 2013; Kimonis et al., 2012, 2013; Mozley et al., 2018; Robertson et al., 2023; Vasileva et al., 2019). According to Kimonis and colleagues (Kimonis et al., 2012, 2013), medium-to-high effect sizes are expected (Cohen’s *d* = 0.41–0.96). Kahn and colleagues (Kahn et al., 2012, 2013) reported small-to-medium effect sizes. Hence, we require an *N* of 84 (ANCOVA; G*Power: effect size = 0.40, α = 0.05, 1−β = 0.95) to estimate the required sample size. To adequately address the research question, an *N* of 84 participants is required. Given a 20% attrition rate, this would correspond to 101.

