In accordance with the study by Neo et al. (2023), the *κ* values will be interpreted using Altman’s (1991) guidelines: values ranging from 0.80 to 1.00 will be classified as indicating very good agreement, values ranging from 0.60 to 0.80 will be classified as indicating good agreement, values ranging from 0.40 to 0.60 will be classified as indicating moderate agreement, values ranging from 0.20 to 0.40 will be classified as indicating fair agreement, and values below 0.20 will be classified as indicating poor agreement. Effect sizes will be estimated using η^2^ (small = 0.01, medium = 0.06, and large = 0.14 (Cohen, 1988)). To correct for multiple testing, Alpha levels will be Bonferroni-Holm corrected.

Before conducting the ANCOVA, a comprehensive series of prerequisite checks will be conducted. These checks encompass the identification of potential outliers (±3 standard deviations), the assessment of linearity between covariate and dependent variables through scatter plots, the evaluation of homoscedasticity via residual plots, and the confirmation of the normal distribution of the disturbance variables through histograms of the standardized residuals and P-P plots. Independence of observations will be addressed through the study design. Multicollinearity is evaluated using variance inflation factors (VIFs). The assumption of homogeneity of regression slopes will be tested by examining the interaction between the grouping variable and the covariate.

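### The stated 95% power does not hold for research question 2 or the correlations at the effects the article expects, nor after the planned Holm correction

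*Protocol article*

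**What the plan says.** All of the sample-size statements are in section 2.4 of the protocol article.

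- **Research question 1, group comparison (ANCOVA).** "we expect medium-to-large effect sizes for research question one when examining and comparing children with and without LPE". The inputs are "effect size = 0.50, α = 0.05, 1−β = 0.95", and the article concludes "that a total sample size of 55 would yield statistically significant results".
- **Research question 1, correlations.** "We expect small-to-medium effect sizes when examining LPE correlations with relevant convergent/divergent constructs". The next sentence begins "Based on calculations (effect size = 0.40, α = 0.05, 1−β = 0.95" and arrives at 63. Sidedness is not given.
- **Research question 2 (ANCOVA).** One group of studies is cited for d = 0.41 to 0.96, with the comment that "medium-to-high effect sizes are expected". A second group is cited for small-to-medium effects. The article then derives N = 84 from an effect size of 0.40, alpha 0.05 and power 0.95. This N becomes the study requirement, raised to 101 for attrition.

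The metric of the 0.50 and 0.40 inputs is not named. In section 2.6, under the effect-size and assumptions heading, the article fixes its own η² benchmarks ("small = 0.01, medium = 0.06, and large = 0.14") and states: "To correct for multiple testing, Alpha levels will be Bonferroni-Holm corrected". It does not say how many tests form a family.

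**The concern.** A power figure is only as good as the effect and the alpha behind it. Here the effects used for research question 2 and for the correlations are larger than much of what the same section says to expect, and the alpha is larger than the one the analysis will use. Both statements stand in this article and do not fit each other, so this is not detail left to a separate analysis plan.

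The correlations matter most for interpretation. Section 1.3 makes statistical significance the criterion for convergent and divergent validity (hypotheses 3 and 4). A reader who trusts 95% power will take a non-significant correlation as evidence against the CAPE, when a true correlation of ordinary size could well have been missed. For research question 2 the risk is that a null result is read as showing that the two variants do not differ.

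**Working it through.** **Inputs.** Effect sizes, alpha, power and N come from section 2.4; benchmarks and the Holm rule from section 2.6. My assumptions are equal groups, all 84 children falling in the comparison concerned, and a Holm family of 5 to 12 tests. Section 2.6 lists nine outcomes for research question 2 if warmth and strictness are counted separately, so 9 is the central value.

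**Step 1: reproduce the ANCOVA figures.** Power = P(F′ > F crit), where F′ is noncentral F with 1 and N − 2 − k degrees of freedom, k covariate terms and λ = f²N.

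- f = 0.50: λ = 0.25 × 55 = 13.75, and N = 55 is the smallest N reaching 95% (54 with no covariate).
- f = 0.40: λ = 0.16 × 84 = 13.44, and N = 84 is the smallest N reaching 95% for every covariate count tried.
- Read as d instead, 0.50 would need 210 and 0.40 would need 327. The inputs are therefore Cohen's f.

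**Step 2: put them on the article's scale.** For two equal groups d = 2f and η² = f²/(1 + f²).

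- f = 0.50: d = 1.00, η² = 0.25/1.25 = 0.20, above the large mark of 0.14.
- f = 0.40: d = 0.80, η² = 0.16/1.16 = 0.138, at the large mark.
- The share of the cited d range at or above 0.80 is (0.96 − 0.80)/(0.96 − 0.41) = 0.16/0.55 = 29%.

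**Step 3: research question 2 at N = 84, alpha 0.05** (k = 3, F crit = 3.96).

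| d | f | λ = f² × 84 | Power | N for 95% |
|---|---|---|---|---|
| 0.41 | 0.205 | 3.53 | 46% | 312 |
| 0.50 | 0.25 | 5.25 | 62% | 210 |
| 0.65 | 0.325 | 8.87 | 84% | – |
| 0.80 | 0.40 | 13.44 | 95% | 84 |
| 0.96 | 0.48 | 19.35 | 99% | 59 |

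The minimum detectable effect at 80% power is about d = 0.62.

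**Step 4: correlations.** Power = Φ(z√(N − 3) − z crit), with z = atanh(r) + r/(2(N − 1)).

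- r = 0.40, N = 63: z = 0.4236 + 0.0032 = 0.4269 (rounded), times √60 = 7.746 gives 3.307. One-sided: 3.307 − 1.645 = 1.662, power 95%. Two-sided: 3.307 − 1.960 = 1.347, power 91%. So 63 is a one-sided figure; two-sided needs 75.
- r = 0.30, N = 63: z = 0.3095 + 0.0024 = 0.3119, times 7.746 gives 2.416. Power is 78% one-sided and 68% two-sided.
- r = 0.30, N = 84: 88% one-sided, 80% two-sided.
- r = 0.20, N = 84: 58% one-sided, 45% two-sided.

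On the usual scale for r, 0.30 is medium. On the article's own variance scale, r = 0.40 explains 0.16, above the large mark of 0.14. Either way it exceeds small to medium.

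**Step 5: first Holm step, alpha/m.**

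| Analysis | m = 5 | m = 9 | m = 12 |
|---|---|---|---|
| f = 0.40, N = 84 | 84% | 79% | 76% |
| r = 0.40, N = 63, one-sided | 84% | 78% | 75% |
| f = 0.50, N = 84 | 97% | 95% | 94% |

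With both issues together, at m = 9 and N = 84, research question 2 has about 30% at d = 0.50 and 17% at d = 0.41.

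**The case against.** Several points on the other side stand.

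- **The stated N are arithmetically right for their inputs.** 55, 63 and 84 all reproduce, so the fault lies in the assumptions and the unused correction.
- **f = 0.40 does not contradict d = 0.41 to 0.96.** It lies inside that range, towards the top. What is missing is cover for the lower part and for the small-to-medium findings cited beside it.
- **The LPE group comparison is adequately sized for its own input.** A reader might infer that all three inputs conflict with small-to-medium expectations. The text does not support this: for f = 0.50 it expects medium-to-large effects. Planning above the large mark leaves the medium end uncovered, but with 84 analysed, f = 0.50 keeps 99.5% uncorrected and about 95% at alpha 0.05/9.
- **The Holm figures are a worst case.** The family size is not stated, and later steps are less strict.
- **Research question 2 is exploratory.** Low power there does not bear on whether the CAPE is valid.

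Two other readings go too far. A reader might infer that d values were typed in as f, because 0.41 is close to 0.40. No d is cited for research question 1 and 0.40 has other possible origins, so this is conjecture. A reader might also extend the effect-size criticism to the hierarchical regression. Its input, f² = 0.15, is medium and matches its text.

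**Conclusion.** The claim of 95% power is wrong as written for research question 2 and for the correlations. For research question 2 at N = 84 it holds uncorrected only from about d = 0.80 upwards, and falls to 62% at d = 0.50 and 46% at the bottom of the cited range. For correlations at r = 0.30 it is 68% to 78% at N = 63 and 80% to 88% at N = 84, depending on sidedness. At the planning effect f = 0.40 itself, the first Holm step leaves about 76% to 84%.

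These figures rest on equal groups, on all 84 children entering the comparison (for research question 2, on 84 with elevated CU traits), on the cited d values being comparable with a covariate-adjusted d, and on an assumed family of 5 to 12 tests. Unequal groups or a smaller subgroup would lower them. The LPE group comparison is not part of the problem at N = 84 for its planned effect.

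**What to change.** Rewrite the sample-size paragraph in section 2.4.

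1. Name the metric of every input (f, d, η² or r), with the conversion, and state whether each test is one-sided or two-sided.
2. For research question 2 and the correlations, replace the 95% claim with power at the planned N over d = 0.41 to 0.96 and r = 0.20 to 0.40. Give it uncorrected and at the first Holm step for a stated family. Alternatively, give the minimum detectable effect: about d = 0.62 at N = 84 with 80% power, uncorrected, equal groups.
3. Delete the statements that a given N would produce significant results; a power calculation gives a probability under an assumed effect.

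The cost is one paragraph and a less favourable power figure. Enrolment, measurements and the analysis methods do not change.

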### 1.3. Working Hypotheses

**Construct Validity of CAPE and LPE**

*Interrater reliability and prevalence*

1.The CAPE interviews are expected to demonstrate moderate to very good interrater reliability.2.It is expected that approximately 50% of children diagnosed with DBD will also exhibit LPE.

*Convergent validity*

3.CAPE will be statistically significantly positively correlated with CU traits, DBD, (proactive) aggressive behavior, and parental strictness.

*Divergent validity*

4.CAPE will be statistically significantly negatively correlated with social competence, empathy, emotion recognition, and parental warmth.

*Incremental validity*

5.The CAPE Interview will demonstrate greater predictive validity than the ICU for DBD, social competence, (proactive) aggressive behavior, empathy, and emotion recognition.

*Group comparison of the specifier “with limited prosocial emotions”*

6.Children with an LPE will differ significantly and positively in CU trait expression, DBD, and (proactive) aggression compared to children without an LPE.7.Children with an LPE will differ significantly and negatively in social competence, empathy, emotion recognition, and parental warmth from children without an LPE.

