**Research question 1:**

*Interrater reliability*

To ascertain interrater reliability, all CAPE interviews will be independently coded by a second rater in a double-blind (no information on questionnaire data and SPJ from the treating clinician) coding process. The secondary coder will either be a psychology student (master’s candidate), a trained child and adolescent psychotherapist, or a trained physician. We will use quadratically weighted Cohen’s κ to estimate interrater reliability.

*Convergent and divergent validity*

Pearson correlations are used to assess discriminative validity (empathy, emotion recognition, parental warmth, social competence) and convergent validity (proactive aggression, DBD, CU traits, aggressive behavior, parental strictness).

*Incremental validity*

Hierarchical regression analyses will be conducted to determine whether the dimensional CAPE score can serve as an incremental predictor of DBD, social competence, proactive aggressive behavior, empathy, emotion recognition, and the control variables of age and gender beyond the ICU.

*Group comparison of the specifier “with limited prosocial emotions”*

This study aims to investigate the hypothesis that children with or without CAPE LPE differ in levels of CU traits, DBD, and social competence, parental warmth/strictness, (reactive/proactive) aggressive behavior, empathy, and emotion recognition. To this end, an analysis of covariance (ANCOVA) will be performed. We will control for age, study site (waiting list, outpatient, daycare, or inpatient), traumatic event, anxiety (to account for primary and secondary CU traits), and sex in the ANCOVA models.

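### The incremental-validity sample size of 83 does not follow from its stated inputs (107 does) or from the test in section 2.6 (89), and the 20% attrition step falls short of the required 84

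*Protocol article*

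**What the plan says.** Section 2.4 of the protocol article gives four sample sizes, all at α = 0.05 and power 0.95:

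- ANCOVA for research question 1: "using G*Power 3.1 (effect size = 0.50, α = 0.05, 1−β = 0.95), that a total sample size of 55".
- Correlations: "Based on calculations (effect size = 0.40, α = 0.05, 1−β = 0.95), we can assume that a sample size of 63 patients".
- Incremental validity: "hierarchical regression (effect size = 0.15, α = 0.05, 1−β = 0.95", with "number of tested predictors: 2; total number of predictors: 7", leading to N = 83.
- ANCOVA for research question 2: effect size 0.40, leading to N = 84.

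The section takes 84 as the required number and raises it for losses: "Given a 20% attrition rate, this would correspond to 101".

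Section 2.6 describes the incremental analysis as a hierarchical regression asking "whether the dimensional CAPE score can serve as an incremental predictor of DBD" and several other outcomes, beyond the ICU, with age and gender as control variables.

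**The concern.** The regression paragraph states every input the calculation needs, so 83 can be checked directly, and it looks too small for two tested predictors at 95% power. Two tested of seven predictors also does not look like the model in section 2.6, where one score is added to three others.

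This regression is the planned test of hypothesis 5, that CAPE predicts better than the ICU. If its N is understated, a null result would be read against a 95% power claim that the design does not deliver.

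The step from 84 to 101 also looks like a 20% mark-up, not an allowance for losing 20% of those enrolled.

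**Working it through.** **Method.** For a fixed-model F test of an R² increase with u tested and p total predictors:

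- noncentrality λ = f²·N
- df1 = u, df2 = N − p − 1
- power = P(F′(df1, df2, λ) > F₀.₉₅(df1, df2))

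The two-group ANCOVA uses the same formula with u = 1 and f² equal to the square of the stated effect size.

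**Step 1: the plan's own ANCOVA figures reproduce.** An effect size of 0.50 gives N = 55 (54 with no covariate). An effect size of 0.40 gives N = 84. The method therefore matches the one the authors used.

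**Step 2: the regression as stated in section 2.4** (f² = 0.15, u = 2, p = 7).

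| N | λ = 0.15·N | df2 = N − 8 | Power |
|---|---|---|---|
| 81 | 12.15 | 73 | 87.3% |
| 83 | 12.45 | 75 | 88.2% |
| 84 | 12.60 | 76 | 88.6% |
| 101 | 15.15 | 93 | 93.9% |
| 107 | 16.05 | 99 | 95.2% |

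At N = 106 the power is 94.97%, so 107 is the smallest N that reaches 95%. The stated 83 is 107 − 83 = 24 short.

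**Step 3: can 83 be recovered another way?** Reading 0.15 as R² (f² = 0.15/0.85) gives 91 for two tested predictors and 76 for one. Testing all seven predictors gives 153. With two tested predictors, power of 0.90 gives 88 and 0.80 gives 68. Values near 83 appear only when two or more stated inputs, or the noncentrality formula, are changed together.

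**Step 4: the test described in section 2.6** (u = 1; p = 4 for age, gender, ICU and CAPE).

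| N | λ = 0.15·N | df2 = N − 5 | Power |
|---|---|---|---|
| 81 | 12.15 | 76 | 93.1% |
| 83 | 12.45 | 78 | 93.6% |
| 84 | 12.60 | 79 | 93.9% |
| 88 | 13.20 | 83 | 94.9% |
| 89 | 13.35 | 84 | 95.1% |

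The required N is 89, and it is the same with p = 7, so the result does not depend on how many control variables are finally listed. The shortfall against 83 is 89 − 83 = 6.

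**Step 5: attrition.**

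- The plan's figure: 84 × 1.2 = 100.8, rounded up to 101.
- What 101 delivers: 101 × 0.80 = 80.8, about 81, which is below 84.
- To keep 84 after a 20% loss: 84/0.80 = 105.
- At 81 evaluable, the f = 0.40 ANCOVA has about 94.5% power.

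**Step 6: correlation.** For r = 0.40 at 95% power, the exact bivariate-normal calculation gives 63 one-sided and 75 two-sided. The stated 63 is the one-sided figure. Two-sided power is 91.1% at 63 and 96.9% at 84.

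**The case against.** **The correlation figure.** A reader who expects two-sided tests might count 63 as a third error and as part of the shortfall. The document does not support that. Hypotheses 3 and 4 state directions, for example "CAPE will be statistically significantly positively correlated with CU traits, DBD, (proactive) aggressive behavior, and parental strictness", so a one-sided calculation is defensible. Even the two-sided 75 lies below 84. All that remains is that sidedness is not declared.

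**What 84 is meant to cover.** A reader might infer that 84, or 101 with attrition, is presented as giving 95% power to every analysis. No sentence says so. The 84 is derived in the research question 2 paragraph and tied to that question. Because 83 sits just below 84, the layout suggests that the regression is covered, but that is an inference.

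**Size of the shortfall.** The 24-participant gap depends on two tested predictors, which section 2.6 does not describe. With one tested predictor, power at 84 is 93.9%, close to target, and 101 with no loss gives 97.1%. A one-sided test of that single coefficient would need only 74. This reduces the practical consequence, but it does not rescue 83, which neither predictor count yields.

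**The predictor list.** Section 2.6 is condensed and the ICU has caregiver and child versions, so the total of four is a reading of the text. The N for one tested predictor does not depend on that total.

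**Attrition.** Data come from one appointment, and the software does not allow completion with missing entries, so 20% may be cautious. That bears on whether 20% is needed, not on how a stated 20% is applied.

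**Conclusion.** The point holds as an arithmetic error and an internal mismatch in section 2.4.

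- The regression N of 83 is wrong for its stated inputs: 107 is needed, and the false-negative risk at 83 is 11.8% instead of 5%.
- It is also wrong for the test in section 2.6, which needs 89. There the loss is only 1 to 2 percentage points of power at 81 to 84 evaluable.
- The 101 should be 105 if 84 governs. The effect on the ANCOVA that sets 84 is about half a percentage point.

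These results assume the fixed-predictor F test, f² = 0.15 as the local effect size, a two-sided test where one predictor is added, and the document's own 20% loss. The error changes no planned analysis. It affects what may be claimed about power for hypothesis 5.

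**What to change.** 1. Reconcile the number of tested and total predictors in section 2.4 with the model in section 2.6, and report the matching N: 89 for one tested predictor, 107 for two.
2. Apply attrition as N/(1 − 0.20) to whichever N governs: 84/0.80 = 105; 89/0.80 = 111.25, so 112; 107/0.80 = 133.75, so 134. Pairing a regression N of 107 with an enrolment of 105 would not be coherent.
3. If recruitment stays at 101, replace the 95% claim for the regression with the power at about 81 evaluable: about 93% for one tested predictor, about 87% for two.
4. Declare the correlation tests as one-sided (63) or two-sided (75). Either is covered by 84.

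The cost is a rewording of section 2.4 and a slightly less favourable power statement. No extra participants are needed if power is restated. Keeping 95% power for the regression after a 20% loss would mean enrolling 11 more (112 − 101) with one tested predictor, or 33 more (134 − 101) with two.
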